### Objectives

In line with current recommendations
[24,25], the objective of this protocol article is to describe the design of a randomized controlled trial, including health economics evaluation and qualitative implementation studies alongside the trial. The design with randomization at two levels makes several comparisons possible (Figure 
1). This study will investigate the effects of short- and long-term inpatient multicomponent rehabilitation programs compared to a single-component intervention and an ‘untouched’ usual care reference group from sick-leave registers. The latter will serve as a reference group to the three interventional groups. The principal objectives are to explore the following research questions:

**Figure 1 F1:**
[figure not shown]
**Design of the study.** ACT: Comparative outpatient Acceptance and Commitment Therapy Rehabilitation group.

• Are the multicomponent rehabilitation programs more effective in reducing sickness absence compared to the single component Acceptance and Commitment Therapy (ACT) program (i.e. Short vs. ACT; Long vs. ACT), and are there differences between the Long and Short programs?

• Are the multicomponent rehabilitation programs cost effective compared to the single component ACT program (i.e. Short vs. ACT; Long vs. ACT)?

• Are the patients’ and service providers’ expectations before participation in the multicomponent rehabilitation programs, in accordance with their experiences afterwards?

• According to the patients’ and service providers’ experiences; have the multicomponent rehabilitation program been implemented as planned?

• Are the multicomponent programs more effective in improving secondary outcomes (e.g. mental or physical health, or motivation for return to work) than the single component Acceptance and Commitment Therapy (ACT) program?

## Methods/design

### Project context

This research project was initiated to evaluate a new occupational rehabilitation centre, Hysnes Rehabilitation Centre (http://www.stolav.no/hysneshelsefort), established as part of St. Olav’s University Hospital. The centre is located in the municipality of Rissa, a 50 min boat ride or 90 min drive from Trondheim, the third largest city (181.500 inhabitants) in Norway. The two multicomponent interventions to be investigated are provided at the rehabilitation centre and consist of a long and a short inpatient program. The control arm, the single component out-patient intervention (see below), is provided at St. Olav’s University Hospital in Trondheim. Earmarked funding from the national budget was provided over a five-year period (2010–2014) to establish and run the rehabilitation programs, inclusive funding for scientific evaluation.

### Design

The study is designed as a randomized controlled trial with three parallel groups and will be reported according to the CONSORT statement
[26]. The study includes health economic- and qualitative aspects. The design is presented in Figure 
1. Monthly extractions of sick listed individuals from The Norwegian Labour and Welfare Service (NAV) with the targeted diagnoses serving as the recruitment base for the study population.

### Study population

Persons living in the counties of Trøndelag, population of 375 000 inhabitants, are eligible for inclusion if they are 18–60 years old and have been on sick leave 2–12 months, with a current sick leave status of 50% - 100%. Individuals with an ICPC-2 (International Classification of Primary Care, Second edition) diagnosis within the L (musculoskeletal), P (psychiatric) or A (unspecific disorders) categories are eligible. Thus both persons being on sick leave due to musculoskeletal and psychological disorders, chronic pain, fatigue and other non-specific disorders are included in the study. Exclusion criteria are: 1) alcohol or drug abuse; 2) serious somatic (e.g. cancer, heart disease) or psychological disorder (e.g. suicide attempts, psychosis, ongoing manic episode); 3) a specific disorder requiring specialized treatment; 4) pregnancy; 5) currently participating in another treatment program; 6) insufficient comprehension of Norwegian language to participate in group sessions and to fill out questionnaires; 7) scheduled for surgery within the next 6 months; and 8) serious problems with functioning in a group setting.

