### Recruitment procedure

NAV provide monthly lists of persons meeting the inclusion criteria. The assigned project co-worker checks eligibility performs the first randomization (Figure 
1) and sends out invitations to potential participants. They receive available information of the project through written leaflets, website of the rehabilitation centre and are invited to call a project co-worker if they have queries. The potential participants are asked to answer a two-page questionnaire and a consent form indicating whether they agree or disagree to take part in the study, or if they require more information. Contacted persons are asked to reply to the project co-worker using an enclosed prepaid envelope. Positive answers are forwarded to the researchers who determine initial eligibility based on the short questionnaire. Prior to enrolment in the study a physician, psychologist and physiotherapist will perform an outpatient assessment of eligibility. Results from the outpatient assessment will be provided to the relevant health personnel and utilized in the rehabilitation program.

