### Outcomes

#### Primary outcome

Total number of sickness absence days during the 6 months after enrolment in the study (i.e. after pre-screening), obtained by national registers.

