### Sample size

Three approaches have been performed to determine sample size:

1) Comparison of number of days with sick leave at 6 months of follow-up (P = 0.05; 90% power): An average of 60 days (SD 40) and 90 days (SD 60) of sick leave in the intervention and comparative group, respectively would require 61 persons for each group.

2) Comparison of time to sustainable RTW with Kaplan Meier survival analysis with log rank test with a hazard ratio of 0.6 (alpha 0.05, beta 0.20) would require 63 in each group (secondary outcome).Comparison of the share of workers after one year with the same statistical assumptions as point 1; 60% versus 40% RTW would require 68 people in each group. (secondary outcome).

Accordingly, with estimated ~20% loss to follow-up we will include 80 persons in each arm.

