### Statistical analyses

Effect analyses of primary and secondary outcomes will be performed according to the intention to treat principle, and per protocol. For the primary outcome, difference in days of sick leave will be evaluated with the Mann Whitney U-test, as sick leave days are unlikely to be normally distributed. Sustainable RTW will be evaluated with survival analysis. Kaplan-Meier analysis will be used to describe association between groups and the duration of absence from work until sustainable RTW. Mixed models will be used to analyze time-dependent health outcomes and to estimate between group differences over time.

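### The primary test of 6-month sickness absence days is unadjusted, although prior sick-leave duration and grade are known at entry; adjusting for them would gain precision and guard against chance imbalance

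*Protocol article*

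**What the plan says.** Under Study population, the protocol article admits people who "have been on sick leave 2–12 months, with a current sick leave status of 50% - 100" per cent, with a diagnosis in one of three ICPC-2 categories. Under Recruitment procedure, "NAV provide monthly lists of persons meeting the inclusion criteria", so duration and grade are on record before either randomization.

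The primary outcome is "Total number of sickness absence days during the 6 months after enrolment in the study", taken from national registers. For its analysis the article says that "difference in days of sick leave will be evaluated with the Mann Whitney U-test, as sick leave days are unlikely to be normally distributed". No covariate or stratum is named. Mixed models are mentioned in the same section, but only for health outcomes followed over time.

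The Sample size section assumes "An average of 60 days (SD 40) and 90 days (SD 60) of sick leave in the intervention and comparative group", with 90% power at 0.05, and concludes that this "respectively would require 61 persons for each group". Allowing for about 20% loss, it plans 80 per arm.

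**The concern.** Entry covers a sixfold range of elapsed sick leave and a twofold range of absence grade. Someone two months into a 50% absence and someone twelve months into a full absence may well have different prospects for the next six months. A plain two-group rank test treats them as interchangeable.

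Two things are then at stake. Outcome variation that baseline could explain stays in the error, which widens the uncertainty of both Long v ACT and Short v ACT. And with about 80 per arm, a chance difference between arms in duration or grade passes into the observed difference without correction. If such an imbalance is noticed afterwards and an adjusted result is then preferred, that choice is post hoc. The remedy has to be fixed in advance.

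**Working it through.** **Inputs.** From the Sample size section: means 60 and 90 days, SDs 40 and 60, alpha 0.05, power 90%, about 20% loss, 80 per arm (64 if 20% are lost). From Study population: duration 2 to 12 months. *Assumptions, not in the document:* duration and grade together explain a share R² = 0.05 to 0.25 of the variance of 6-month days; elapsed duration is uniform over 2 to 12 months.

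**1. The plan's own figure.** Common SD = √((40² + 60²)/2) = 50.99. With a two-sided test, n = 2 × (1.960 + 1.282)² × 50.99² / 30² = 60.7, so 61 per group. The stated 61 is reproduced, and it comes from an unadjusted two-means formula.

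**2. Value of adjustment.** Linear adjustment reduces the SD to 50.99 × √(1 − R²), which is worth a factor 1/(1 − R²) in participants. Power is Φ(δ / (SD × √(2/m)) − 1.96), with m analysed per arm.

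| R² | 1/(1 − R²) | SD | n per group, 90% power | Power, δ = 30, m = 64 / 80 | Power, δ = 20, m = 64 / 80 |
|---|---|---|---|---|---|
| 0 (unadjusted) | 1.00 | 50.99 | 61 | 91.4% / 96.1% | 60.2% / 69.9% |
| 0.05 | 1.05 | 49.70 | 58 | 92.7% / 96.8% | 62.4% / 72.1% |
| 0.10 | 1.11 | 48.37 | 55 | 93.9% / 97.5% | 64.8% / 74.4% |
| 0.20 | 1.25 | 45.61 | 49 | 96.1% / 98.6% | 69.9% / 79.2% |
| 0.25 | 1.33 | 44.16 | 46 | 97.0% / 99.0% | 72.6% / 81.7% |

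These are normal approximations for a difference in means, used to show the relative gain. They are not exact powers of a rank test.

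**3. Chance imbalance in duration.** The SD of a uniform variable over 2 to 12 is 10/√12 = 2.89 months. The standard error of the difference between arms is 2.89 × √(2/80) = 0.46 months, so the 95% range is ±0.9 months. With 64 per arm it is 0.51 and ±1.0 months. A gap of more than half a month has a chance of about 27% (80 per arm) or 33% (64 per arm).

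**4. In outcome days.** Take the best linear combination of duration and grade. An imbalance at its 95% limit moves the unadjusted difference by √R² × 50.99 × 1.96 × √(2/m). With m = 80 that is 3.5 days at R² = 0.05 and 7.9 days at 0.25; with m = 64 it is 4.0 and 8.8 days. The planned effect is 30 days. These are limits, not typical values: the standard deviation of the shift is the limit divided by 1.96, so about 1.8 to 4.0 days with m = 80.

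**5. Validity.** In a simulation of 4,000 trials per setting, with the outcome bounded at 0 and 183 days and 64 per arm, the rejection rate under no effect was 4.6% to 5.4% for Mann-Whitney and 4.7% to 5.1% for rank ANCOVA. Both hold their level. The powers from that simulation depend on an invented distribution and should not be read as this trial's power.

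**The case against.** The strongest reply is that nothing here is an error. Randomization makes the Mann-Whitney test valid without covariates, and chance imbalance is already part of its null distribution. A reader might infer from the broad entry criteria that the primary result is biased or its p-value unreliable. The document does not support that: type I error is protected, and the heterogeneous population is deliberate, as the Background and Strengths sections explain. This part of the reply stands.

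The prognostic strength also has no source in the document. Duration is truncated to 2 to 12 months, and those enrolled have volunteered and passed a clinical assessment, which may weaken any relation. A reader might go further and treat prior duration and grade as the outcome itself measured earlier. That is not supported either: the outcome is a count of days, and the article does not say whether days are weighted by grade. Both points stand and are why a range is shown, starting at R² = 0.05.

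Power at the planned effect is ample, as the reply also says. The primary outcome comes from registers that include non-responders, so the number analysed may be nearer 80 than 64. The case for adjustment therefore rests on smaller true effects, which are plausible because the comparator is itself an active ACT program, and on protecting the estimate.

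Finally, a reader might infer that the second randomization is unstratified and ask for strata. The article is silent on this, and an article commonly leaves it to the full protocol. No finding follows.

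What the reply does not remove is that the article names a specific unadjusted primary test. A supporting adjusted analysis in an unseen plan would leave the primary p-value resting on that test.

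**Conclusion.** The point holds as one of efficiency and robustness to chance imbalance, not of validity. The named primary test leaves unused two baseline variables that the trial already holds and that plausibly predict the outcome. If they explain 5% to 25% of its variance, which is an assumption, adjustment is worth about 5% to 33% more participants. It adds roughly 1 to 6 percentage points of power at a 30-day difference and 2 to 12 at a 20-day difference. If the true R² is near the lower end, little is lost by leaving the test as it is.

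**What to change.** Under Statistical analyses, pre-specify one covariate-adjusted rank-based analysis as primary for Long v ACT and for Short v ACT. Either rank ANCOVA or a proportional-odds model for days would do; choose one and name it. The covariates are register sick-leave duration, kept continuous, and absence grade. Duration should not be cut into two groups: under the uniform assumption with a linear relation, a split at 6 months (40% below, 60% above) keeps only 3 × 0.4 × 0.6 = 72% of its information.

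Take both covariates at the last register value before the second randomization. Invitation, reply and outpatient assessment intervene after the monthly extraction, so the list values may be out of date by then. Keep the unadjusted Mann-Whitney test as a sensitivity analysis.

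The cost is small: an added modelling assumption, which the sensitivity analysis makes visible, and the work of extracting the two values at a defined date. No extra participants or questionnaires are needed, and the randomization is unchanged.

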### Recruitment procedure

NAV provide monthly lists of persons meeting the inclusion criteria. The assigned project co-worker checks eligibility performs the first randomization (Figure 
1) and sends out invitations to potential participants. They receive available information of the project through written leaflets, website of the rehabilitation centre and are invited to call a project co-worker if they have queries. The potential participants are asked to answer a two-page questionnaire and a consent form indicating whether they agree or disagree to take part in the study, or if they require more information. Contacted persons are asked to reply to the project co-worker using an enclosed prepaid envelope. Positive answers are forwarded to the researchers who determine initial eligibility based on the short questionnaire. Prior to enrolment in the study a physician, psychologist and physiotherapist will perform an outpatient assessment of eligibility. Results from the outpatient assessment will be provided to the relevant health personnel and utilized in the rehabilitation program.

### The three occupational rehabilitation interventions

The three intervention programs: Long and Short multicomponent in-patient programs and the single component program are developed through cooperation between health care personnel and the research group and have all been piloted. All health personnel delivering the interventions were given training in ACT prior to and during (monthly) the intervention by the same certified ACT-supervisor. See Table 
1 for an overview and comparison of the programs.

**Table 1 T1:** Overview of the three rehabilitation programs

	**Long multicomponent program**	**Short multicomponent program**	**ACT comparative arm**
*Setting*	Inpatient rehabilitation center	Inpatient rehabilitation center	Outpatient Hospital clinic
*Duration*	3.5 weeks	4 + 4 days, separated by 2 weeks living at home	6 weeks
*Contents and quantities*	-group discussions (×8, total 16 h; ACT based)	-group discussions (×6, total 12 h; ACT based)	-ACT group discussions (×6, total 15 h)
	-psychoeducational sessions (×4, total 6.5 h)	-psychoeducational session on stress (×1, 2 h)	-group discussion on physical activity (×1, 1 h)
	-individual meetings with coordinator (×5, total 5 h)	-individual meetings with coordinator (×2, total 2 h)	-individual sessions with social worker (×2, total 2 h)
	-individual meeting with physician (×1, 0.5 h)	-individual meeting with physician (×1, 0.5 h)	-individual session with social worker and ACT group moderator (×1, 0.5 h)
	-mindfulness sessions (×7, total 3.5 h)	-mindfulness sessions (×4, total 2 h)	-home practice, including daily mindfulness
	-individual/group based supervised training sessions (×10, total 12 h)	-individual/group based supervised training sessions (×8, total 10.5 h)	
	-“walking to work” (×6, total 3 h)	-Create RTW-plan	
	-Create RTW-plan	In the 2 weeks between the stays at the rehab:	
	-outdoor activities day (×1, 5 h)	-Meeting with employer, if relevant and permitted	
	-“network day” with 2 group sessions (total 4 h)	-At least 2 contacts with team coordinator (telephone or personal)	

All references to time are average estimates, which may include short breaks in and between sessions. ACT: Acceptance and Commitment Therapy. RTW: Return-to-work.

*The Long and Short multicomponent programs* are both individual and group-based with maximum eight participants in each group organized as a six-seven-hour workday at the inpatient rehabilitation center. The Long program lasts ~3.5 work weeks (17 days) and the Short program lasts 4 + 4 days separated by 2 weeks where participants live at home. In both programs, 2–3 designated RTW coordinators per group are involved in coordinating and executing the interventions. Three areas of rehabilitation are targeted: mental training, physical training and work-related problem solving. The coordinator’s backgrounds are diverse (physical therapy, psychology, and exercise physiology, nursing or other). Each coordinator is responsible for mentoring two or three participants during the intervention. There are three multidisciplinary team meetings, where both health personnel in the Long and Short programs attend, discussing strategies concerning the participants’ obstacles and possibilities for increased work participation (total 5, 5 hours).

*The mental training*, aims to increase the participant’s psychological flexibility, motivation and self-efficacy, and reduce sickness absence. The intervention manuals are based on ACT (Acceptance and Commitment Therapy)
[27], an evidence-based cognitive-behavioral approach. The therapeutic model in ACT is founded around six dynamic processes: committed action, self-as-context, presence in the moment, values, defusion and acceptance. These processes are targeted both in group-sessions and individual meetings. To ensure that all six processes are addressed in the group-sessions, the coordinators evaluate which of the processes they have targeted after each session. Commitment, value-based actions, and being mindful are intended to increase motivation and efficacy with regard to work. The mental training consists of group sessions, psycho-education (stress, pain and symptom interpretation, nutrition, and sleep in the Long program, and only on stress in the Short program). Further, mindfulness training and individual homework are given in all programs.

*The physical training* intervention aims to increase physical strength and endurance capacity and to promote physical activity, whilst also improving knowledge about physical activity. It also targets fear of movement, tension-related pain, and a “normal” pattern of movement. Each participant starts their stay developing a personalized physical activity plan in cooperation with their coordinator and the designated exercise coach. The teaching and training sessions are both individual and group-based. The exercise program is individualized based on clinical judgment, and the goals and wishes of the participant. The exercise coach regularly evaluates the participant’s progress. Participants are given training programs when leaving the center.

*The work-related problem-solving* aims to identify challenges and possibilities, increase readiness for work and ways to adopt these strategies in daily life after the stay at Hysnes rehabilitation center. This is performed as part of the group sessions and in the individual meetings with the coordinator. This intervention aims to motivate the participant, clarify the value of work, to highlight participants’ challenges and resources, and to make a realistic plan for increasing their work participation. This plan is being worked on throughout the rehabilitation stay. Moreover, the crossover from Hysnes Rehabilitation Center to re-enter work and home life is addressed. Stakeholders in the rehabilitation process are included in the process: midway and discharge summaries are sent to the participant’s general practitioner in all cases, and to the social security office and employer, depending on relevance and the participants’ consent. Furthermore, there are different stakeholder-involvement in the Short and Long program, as described below.

*Differences between the Long and Short programs*. In addition to differences in duration and amount, there are some content differences between the Long and Short multicomponent programs. In the Long program a “network day” is arranged where the participant can bring one or several persons (usually family, physician or close friends) to gain insight in the rehabilitation process, in order to facilitate support after the end of the program. In the Short program, a workplace visit is arranged if relevant and supported by the participant, either between the two rehabilitation stays or after the stay at Hysnes rehabilitation center. The purpose of this visit is to identify barriers and solutions for RTW. If the participant currently has no job, a meeting with The Social Security Office (NAV) may be conducted instead. The general practitioner can also attend if relevant. Meetings are usually performed in person, but can also be arranged via video or telephone conference. While participants in the Short program are at home, the coordinator and participant have at least two contact points.

*The single component ACT comparison intervention* is provided in the context of an established musculoskeletal outpatient specialist unit at the Physical Medicine and Rehabilitation (PM&R) department at St. Olav’s University Hospital. This program is an outpatient group intervention using ACT in groups following a manual especially designed for this study.

A maximum of nine participants are invited to attend group-sessions once a week for six weeks. One of two physicians (both PM&R specialists) or a psychologist all specifically trained in ACT is in charge of the group sessions. Home practice is encouraged between sessions including 15 min daily mindfulness practice. In addition, an experienced social worker with training in occupational rehabilitation and ACT offers two individual sessions. The individual sessions aim to clarify personal values and problem solving issues if considered relevant for increased work participation. Participants are also invited to take part in a physiotherapist lead group discussion on benefits and motivational factors for physical exercise. Physical exercise is not included in the intervention.

The intervention ends with an individual session with both the social worker and the ACT group moderator present. In this session the participant contributes to and approves a final summary letter addressed to the general practitioner. The letter summarizes the intervention content, the participant’s experiences during the six weeks and future plans of action. No further steps are made for coordination between stakeholders. Participants are encouraged not to start any new treatment during the intervention but are allowed to continue any concurrent treatment at the discretion of the general practitioner.

